## Abstract

**Background:**

Alcohol withdrawal syndrome (AWS) constitutes a critical clinical outcome across the spectrum of alcohol use disorders (AUD), comprising severe neuropsychological manifestations during early abstinence among individuals with alcohol dependence. Pharmacological management primarily relies on benzodiazepines, which may cause dependence and hepatic stress. Addressing the core psychological domains is essential for uplifting the quality of life in such patients, and an integrated psychopharmacological approach rooted in holistic principles would be prioritized for better recovery. Ayurveda believes in treating the root cause rather than the symptoms, and hence, a polyherbal formulation is used in this trial, which would act on the doshas (humors) responsible for the manifestation of AWS. Hence, integrating the therapeutic intake of *Kharjuradi Mantha* coupled with mind–body relaxation interventions could provide substantial symptom control and enhanced recovery outcomes.

**Objectives:**

This exploratory randomized study protocol aims to evaluate the efficacy of a therapeutic herbal infusion (*Kharjuradi Mantha*) as an adjunct to multidisciplinary relaxation techniques comprising yoga, meditation, and counseling in individuals experiencing mild-to-moderate AWS.

**Methods:**

An exploratory, open-label, parallel-group randomized controlled trial will be conducted among 38 male inpatients who are diagnosed with mild-to-moderate AWS (Clinical Institute Withdrawal Assessment for Alcohol–Revised [CIWA-AR] score 8–15). Participants will be randomly assigned in a 1:1 ratio to receive either the herbal infusion in addition to relaxation techniques or the relaxation techniques alone for 28 days. The major outcome measure is to evaluate the difference in CIWA-AR scores from baseline to the 29th day after the completion of the trial in the trial setting.

**Expected outcomes:**

It is anticipated that the herbal infusion will enhance symptom resolution and overall psychological stability, which is reflected in the CIWA-AR scores when combined with yoga, meditation, and counseling, compared with standard non-pharmacological management alone.

**Clinical trial registration:**

https://ctri.nic.in, Identifier CTRI/2024/07/070952.

## Introduction

1

Alcohol dependence remains a global health challenge, contributing to more than three million deaths annually and representing approximately 5% of the total global disease burden (1). Alcohol withdrawal syndrome (AWS) is a practically alarming ramification occurring due to intentional or unintentional sudden and abrupt cessation of binge drinking in patients suffering from alcohol use disorders (AUD) (2). Recent studies have indicated that up to 50% of patients with AUDs will experience AWS manifestations leading to substantial morbidity and mortality, along with approximately 5.1% of disability-adjusted life years (DALYs) (3). During early abstinence, individuals with AWS may present with minor-to-moderate systemic symptoms with the involvement of psychological domains such as headache, mild anxiety, insomnia, gastrointestinal discomfort, tremors, restlessness, sweating, and sleep disturbances. However, if untreated, these symptoms can progressively worsen into severe complications such as delirium tremens and withdrawal seizures, posing significant clinical risks4. Diagnosis and management can be challenging because of potential barriers in relation to accessibility and availability of services, as well as the public stigma, which discourages individuals to seek help or treatment.

The current management strategies primarily rely on benzodiazepines and supportive care to stabilize neurological and autonomic disturbances (4). Even though the protocol has been found to be effective in reducing acute symptoms, these pharmacological agents might often interact with ethanol, resulting in respiratory distress along with other effects such as sedation, dependence, and hepatic stress (4). Moreover, they do not adequately address the psychological domains of AWS, including craving, emotional instability, and relapse risk, which are vital in a sustained recovery.

Ayurveda is an indigenous, holistic, and culturally rooted medical system that has been widely practiced in the Indian subcontinent for centuries, with an extensive pharmacopeia for managing a wide range of ailments prevalent in the community. This system has emphasized the core concept of balance, wherein the cardinal etiology for the majority of the pathologies has been attributed to improper lifestyle regimens. Similarly, it has placed emphasis on an optimal amount of alcohol intake (Madyapaana), and one who indulges in irresponsible drinking would be contracted with loss of ojas (vital essence), leading to a condition called Madatyaya (alcoholic intoxication). Madya (Alcohol) possesses almost similar gunas (qualities) to visha (toxin) and may act similar to a toxin once it enters the body (5), thereby vitiating the dhatus (bodily tissues) and ojas present in the Hridaya (organ which is the root of rasavaha srotas and ojas, similar to heart). Abnormal levels of Madya may augment the intrinsic homologous qualities (guna) within the body, thereby impacting the equilibrium of vital humors or doshas. As Madya possesses ruksha (dry) and tikshna (sharp) qualities (6) it could essentially surge the normal levels of vata and pitta dosha (humors) as well. Clinically, these disproportionately higher levels of doshas should be counteracted with the opposite gunas. The resultant manifestations might continue even in the absence of alcohol, which would essentially require target-specific management prioritizing the Madya gunas and vitiated dosha-dhatus. Hence, a therapeutic polyherbal formulation, Kharjuradi Mantha, which can counter the vitiated doshas by imparting santarpana, i.e., a therapeutic nourishment to the vitiated body elements, has been selected in this study (7). Moreover, recent ethnopharmacological studies have demonstrated that *Phoenix dactylifera* (date fruit) and other nutritionally rich ingredients in Kharjuradi Mantha offer multiple restorative effects, including antioxidant and neuroprotective effects in alcohol-related oxidative stress and neuronal dysfunction (8). The spectrum of physical symptoms is intermingling with psychological features in all the stages, thereby manifesting emotional and behavioral decline in the patients of Madatyaya. Recent research evidence emphasizes that complementary interventions, particularly those involving mind–body relaxation techniques, have demonstrated promising results in improving emotional regulation, reducing craving, and promoting abstinence (9). Yoga, meditation, and counseling are widely recognized for their ability to modulate stress pathways, enhance parasympathetic activity, and support behavioral transformation during de-addiction therapy (10, 11). Moreover, the majority of rehabilitation centers in India follow the National Action Plan for Drug Demand Reduction (NAPDDR) Guidelines, which establish the fact that counseling and other relaxing techniques should be included under a standard protocol in such centers for mild-to-moderate AWS (12).

Despite the rising scopes in integrative approaches, there remains a significant lack of substantial clinical evidence evaluating the combined effect of therapeutic herbal remedies and structured relaxation techniques in the management of AWS. This phase will be more pronounced with uncomplicated physical symptoms and persistent appearance of psychiatric symptoms, which also need to be addressed as an area of greater concern. Hence, an evidence-based integrated protocol that targets both dimensions in an uncomplicated manner will help in reducing symptoms, thereby preventing their progression to a severe stage and uplifting the quality of life in the patients of AWS.

This exploratory randomized study protocol has been designed to inspect the efficacy and feasibility of an herbal infusion (Kharjuradi Mantha) administration when integrated alongside relaxation techniques such as yoga, meditation, and counseling, compared with relaxation techniques alone in the management of AWS. This trial aims to provide scientific evidence supporting an integrative, culturally compatible model for alcohol withdrawal management.

## Methods and analysis

2

This study protocol has been drafted by adhering to SPIRIT (Standard Protocol Items: Recommendations for Interventional Trials) guidelines (13).

### Study design

2.1

This is an open-label, parallel-group, exploratory randomized controlled trial designed to evaluate the efficacy and safety of a therapeutic polyherbal infusion (Kharjuradi Mantha) as an adjunct to multidisciplinary relaxation techniques in the management of mild-to-moderate AWS.

In the present study setting, multidisciplinary relaxation techniques constitute the baseline standard of care in the management of mild-to-moderate AWS in accordance with NAPDDR Guidelines. In moderate cases, these interventions will be continued under strict monitoring with a protocol for escalation to pharmacological management if required. A similar pre-defined pharmacological protocol with benzodiazepines is in place, and patients requiring such management will be excluded at baseline or managed accordingly by adopting the rescue medication strategy. This protocol does not aim to replace standard pharmacotherapy; however, it aims to evaluate the efficacy of the polyherbal infusion as an adjunct to the standard supportive care in patients with mild-to-moderate AWS.

### Study setting

2.2

The trial will be conducted at the Spandana Integrated Rehabilitation Centre for Addicts (IRCA), Harihara, Karnataka, India.

### Study population

2.3

According to the Diagnostic and Statistical Manual of Mental Disorders, Fifth Edition (DSM-5) criteria, participants who are male inpatients aged 25–60 years and diagnosed with mild-to-moderate AWS will be recruited for this trial11.

### Eligibility criteria

2.4

The inclusion criteria for this trial include male participants aged between 25 and 60 years, those who are diagnosed with mild-to-moderate AWS (CIWA-AR score 8–15) (14), those who are willing to participate and provide written informed consent, and residents who are already undergoing non-pharmacological management for alcohol withdrawal. Patients with severe withdrawal (CIWA-AR > 15) or delirium tremens, hepatic failure, ischemic heart disease, or uncontrolled metabolic disorders; those who are currently on psychotropic or hepatotoxic medication; those who are diagnosed with any major psychiatric disorders; or those who are in concurrent participation with another clinical trial will be excluded from the study.

All participants will be strictly monitored and continuously evaluated for the progression of symptoms into a severe stage, where a predefined rescue medication protocol will be adopted for conventional management in such cases.

### Recruitment

2.5

Participants will be recruited from the inpatient population of Spandana IRCA through clinician referrals and screening of eligible cases. Written informed consent will be obtained before enrolment. Patients will be added one at a time until the target sample size is achieved.

### Interventions

2.6

After admission, each patient will be given a 2–3-day adjustment period, depending on their mental status, to help them acclimatize to the environment. Following this, the inclusion and exclusion criteria will be assessed. The study details will be explained thoroughly, and only those patients who are willing to participate will be considered for enrolment. Before initiation of the trial, the CIWA-AR scale will be administered. Patients scoring less than 15, indicating mild-to-moderate alcohol withdrawal symptoms, will be confirmed as suitable candidates for the study. After obtaining their consent and explaining all trial procedures, these patients will be included in the trial. The ingredients will be botanically identified, and the infusion sample will be prepared from a CARE KERALAM GMP-certified company. The preparation will be replicated daily at the rehabilitation center under the direct supervision of a qualified quality pharmacy supervisor, strictly adhering to the master formula record and SOP established at CARE KERALAM. From day 1, participants in the trial group (Group A) will receive 50 mL of the Kharjuradi Mantha twice daily, administered 30 min before breakfast and dinner, along with 1 h of Yoga and meditation in the morning and 1 h of counseling daily. Ingredients mentioned for the polyherbal infusion Kharjuradi Mantha are mentioned in Table 1, and the general method of preparation and details of administration are demonstrated in Figure 1 and Table 2, respectively. The counseling sessions will be conducted by experts from the counseling department, while yoga and meditation sessions will be carried out by trained professionals. In the control group (Group B), patients will undergo yoga, meditation, and counseling only, without the formulation. The details of the intervention plan that will be followed in both groups have been provided in Tables 3, 4.

**Table 1 tab1:** Ingredients of polyherbal infusion *Kharjuradi Mantha.*

Sl. No.	Ingredients	Quantity
1	*Kharjura (Phoenix dactylifera)*	1 part
2	*Mrdveeka (Vitis vinifera)*	1 part
3	*Vrikshamla (Garcina indica)*	1 part
4	*Amlika (Tamarindus indica Linn)*	1 part
5	*Dadima (Punica granatum)*	1 part
6	*Parushaka (Grewia asiatica Auct)*	1 part
7	*Amalaki (Phyllanthus emblica)*	1 part
8	Water	4 parts

**Figure 1 fig1:**
[figure not shown]
Method of preparation of *Kharjuradi Mantha.*

**Table 2 tab2:** Details of the administration of management.

Parameter	Details
Form	Freshly prepared *Kharjūrādi Mantha*
Dose	100 mL in two divided doses before breakfast and dinner (dose fixation according to classical reference)
Time of administration	Twice a day before food
Vehicle of administration	Water
Duration	For 4 weeks (28 days)

**Table 3 tab3:** Planned administration details of yoga and meditation in both groups.

Sl. No.	Type of practice	Practices		Duration
1	Prayer	Starting yoga with prayer		
2	Loosening practices	Fingers (clench fist and open), wrist (bending and rotation), elbow movements, shoulder rotation, neck movements (up-down, right and left movements), hip loosening exercise, knee flexion, ankle movement, toes movement		10 min
3	Breathing practices	*Anuloma viloma pranayama, ujjayi pranayama, bhramari pranayama*		10 min
4	*Yogasana* (simple yogic poses)	4.a	*Surya namaskara* (sun salutations)	10 min
		4.b	*Tadasana* (palm tree pose), *kateechakrasana* (standing spinal twist), *vrikshasana* (tree pose), *simhasana* (lion pose), *ardha matsyendrasana* (half spinal twist pose), *bhujangasana* (cobra pose), *shalabhasana* (locust pose), *dhanurasana* (bow pose), *pavanamuktasana* (wind- relieving pose), *vipareeta karani* (legs-up-the-wall pose) with *uddiyana bandha* (abdominal lock) and *moola bandha* (root lock), *shavasana* (corpse pose)	25 min
5	Meditation	“om” chanting		5 min
Total duration 60 min				

**Table 4 tab4:** Counseling session plan for both groups.

Type of counseling	Duration	Description
Individual counseling	1 h/session/day	One-to-one session with a counselor focusing on abstinence benefits, illness understanding, ill-health effects, social problems, motivation building, coping skills, and relapse prevention.
Family counseling	Weekly-1 h	Session with parents/partner explaining the importance of family support, communication improvement, identifying triggers at home, and helping the patient maintain abstinence.
Mass/group counseling	Weekly-1 h	Group session for sharing experiences, peer motivation, relapse prevention education, building confidence, and social support

The trial methodology plan is given in Figure 2 and shows the detailed grouping, intervention, and assessments in the trial. This protocol will be followed for 28 days. On the 29th day, the CIWA-AR scale will be reassessed to evaluate post-intervention changes.

**Figure 2 fig2:**
[figure not shown]
The trial methodology plan.

### Outcome measures

2.7

The major outcome measure is to evaluate the changes in the CIWA-AR score from baseline to Day 28 to assess and diagnose the severity of alcohol withdrawal. The CIWA-AR scale has been a reliable and relevant tool in AWS, especially in clinical scenarios, where it has a sensitivity of 47% at a 95% confidence interval and a specificity of 88%, which makes it a reliable tool for assessment (15).

### Participant timeline

2.8

Participants enrolled in the study will undergo three progress evaluations, as demonstrated in the planned schedule chart in Table 5. These evaluations encompass the gathering of preliminary information, administration of the intervention, and pre-post assessments. During the first evaluation (Day 0), screening and recruitment of patients will be conducted following diagnosis, along with assessment of eligibility criteria. Patients who do not meet the eligibility criteria or who are unwilling to participate will be excluded from the study. Eligible patients will be assessed using the CIWA-AR scale. On the same day, randomization will be performed using the lottery method, thereby allocating patients to either the study group or the control group, and the corresponding management will be initiated. During the second evaluation, progress will be reviewed after approximately 2 weeks, with specific attention to any adverse events in both groups. During the final evaluation (Day 29), both groups will be reassessed using the predetermined assessment criteria, and the findings will be documented for statistical analysis.

**Table 5 tab5:** Planned schedule chart for each participant in the trial.

Trial events	Day 0	2nd week	4th week (Day 29)
Screening & recruitment with informed consent	✓		
Inclusion & exclusion criteria assessment	✓		
Diagnostic criteria assessment	✓		
CRF filing/Physical examination	✓		
Randomization and allocation	✓		
CIWA-AR Assessment	✓		✓
Patient education	✓		
Review of adverse events		✓	✓

### Sample size calculation

2.9

As it is an exploratory clinical trial, it exceeds common rules of thumb for these studies (≥ 12 per arm), and after considering non-probability/convenience sampling measures, the study sample size was determined as 38, with 19 participants each in the study group and control group for a trial period of 28 days.

### Randomization and allocation concealment

2.10

Participants will be randomly assigned in a 1:1 ratio to either the study or control group using a simple randomization method (sealed chit system).

Allocation concealment will be maintained through opaque, sequentially numbered envelopes opened only after participant enrolment. The enrollment number of the participants will be printed on the top of the envelope, and a slip indicating the group will be kept inside the envelope. After the recruitment and collecting the baselines, the researcher will provide the envelope to the participants in the order of their enrollment number. After opening the envelope, participants will be allocated to the corresponding group as indicated on the slip.

### Blinding

2.11

Due to the distinct appearance and taste of the herbal infusion, participant and investigator blinding is not feasible. However, data analysts and outcome assessors will remain blinded to group allocation for reducing bias.

### Data collection and management

2.12

All the baseline data collected will be mentioned in the case file and in a case report form (CRF), which is specific for each participant, comprising history, examinations, and assessment scales. CIWA-AR is a 10-step questionnaire with well-documented reliability, reproducibility, validity, and feasibility in clinical settings and has been administered here to assess the symptoms. Trial adherence will be assured by scheduling subsequent visit reminders, and the follow-up data will be mentioned in the case file as well as the CRF. Even if a patient wants to withdraw from the trial or if they are not complying with the treatment, the case file and CRF will be documented for record purposes.

Data entry will be done as a soft copy in secured databases and recorded manually as a hard copy in the CRF. The values will be cross-checked by the co-investigator before uploading into the database, and all the data will be rechecked before submitting for final analysis.

### Statistical analysis

2.13

Statistical analysis will be performed using IBM SPSS version 29.0 software. Data will be analyzed using appropriate statistical measures, including paired *t*-tests for within-group comparisons and independent *t*-tests for between-group comparisons, assuming normal distribution of data. Repeated-measures ANOVA will be applied to assess changes over time in multiple groups based on the nature of data, and outcome measures. A *p*-value of < 0.05 will be considered significant.

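### The between-group comparison in 2.13 is not adjusted for baseline CIWA-AR, although everyone has that score; ANCOVA would use it at almost no cost

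*Protocol article*

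**What the plan says.** Protocol article, 2.13 (Statistical analysis), gives paired t-tests within groups and independent t-tests "for between-group comparisons, assuming normal distribution of data". It adds that "Repeated-measures ANOVA will be applied to assess changes over time in multiple groups" and that a p-"value of < 0.05 will be considered significant". It names no covariate and no regression model, and it does not say whether the independent t-test is run on change or on final scores.

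The outcome in 2.7 is worded as change: "The major outcome measure is to evaluate the changes in the CIWA-AR score from baseline to Day 28". The Abstract also describes a difference from baseline, to the 29th day. In 2.8, "Eligible patients will be assessed using the CIWA-AR scale" at Day 0, with randomisation on the same day. Table 5 shows CIWA-AR at Day 0 and Day 29 only.

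On size, 2.9 states that "the study sample size was determined as 38, with 19 participants each in the study group and control group". Section 2.10 describes simple 1:1 randomisation by sealed chits and mentions no stratification.

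**The concern.** The trial has one outcome scale, 38 participants, and a baseline value of that scale for each of them. An independent t-test does not use that value as a covariate. On change scores it subtracts the whole baseline, which over-corrects whenever the regression of Day-29 score on baseline has a slope below 1. On Day-29 scores it ignores the baseline. Either way, the estimate shifts with a chance difference between the arms at entry, and the two versions shift in opposite directions.

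Two things are at stake: precision in a very small trial, and how a result can be read if the arms start visibly apart. Because 2.13 leaves the choice of score open, that choice could also be made after the imbalance is known.

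**Working it through.** **Inputs from the article.** 19 per arm, N = 38 (2.9); alpha 0.05 (2.13), taken as two-sided because sidedness is not stated; CIWA-AR at Day 0 and Day 29 (Table 5); simple randomisation (2.10); entry range 8–15 (2.4).

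**Assumptions, not in the article.** Correlation r between baseline and Day-29 scores, shown as a range; equal SDs at the two times, relaxed in step 6; a true difference of 0.93 SD, for illustration only.

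**1. The plan's own figure.** The article gives no effect size, SD, power or dropout, so 38 cannot be reproduced as a calculation. The stated basis is that "it exceeds common rules of thumb for these studies", meaning at least 12 per arm. That gives 2 × 12 = 24, a floor and not a derivation. With 19 per arm, a two-sided t-test has 80% power at a difference of about 0.93 SD.

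**2. Does the repeated-measures ANOVA help?** With two timepoints and two groups, the group-by-time F equals the squared t of the change-score test. A simulated dataset with 19 per arm confirmed it: F = 3.369, t² = 3.369. It is the same unadjusted analysis.

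**3. Size of chance imbalance.** The SD of the difference in baseline means is sqrt(2/19) = 0.324 SD, so the 95% range is ±1.96 × 0.324 = ±0.64 SD. A gap above 0.33 SD occurs in about 31% of such trials. If baseline scores were uniform over 8–15 (assumed SD 2.29), ±0.64 SD is about ±1.46 points.

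**4. How much reaches the estimate.** For a baseline gap g, the expected Day-29 gap without any treatment effect is r·g, and the expected gap in change is r·g - g = -(1-r)·g. ANCOVA removes it. At g = 0.64 SD:

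| r | shift, Day-29 test | shift, change test | conditional error, Day-29 | conditional error, change |
|---|---|---|---|---|
| 0.3 | 0.19 SD | -0.45 SD | 8% | 16% |
| 0.5 | 0.32 SD | -0.32 SD | 13% | 13% |
| 0.7 | 0.45 SD | -0.19 SD | 20% | 10% |

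The error columns use a normal approximation and hold given a gap at the edge of the 95% range. At a typical gap of 0.32 SD the conditional error stays at about 4–5% in every case.

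**5. Precision.** Variance of the estimated difference, relative to a Day-29 t-test: Day-29 = 1; change = 2(1-r); ANCOVA = (1-r²)(1 + 1/(N-4)) = (1-r²) × 35/34, where 35/34 is the cost of estimating the slope.

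| r | ANCOVA / change | ANCOVA / Day-29 | power at 0.93 SD: change, Day-29, ANCOVA |
|---|---|---|---|
| 0.1 | 0.57 | 1.02 | 55%, 80%, 79% |
| 0.3 | 0.67 | 0.94 | 66%, 80%, 82% |
| 0.5 | 0.77 | 0.77 | 80%, 80%, 89% |

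The second column is (1+r)/2 × 35/34; for example 0.65 × 1.029 = 0.67 at r = 0.3. Break-even against the Day-29 test is r² = 1/35, so r = 0.17. Against the change-score test, (1+r)/2 × 35/34 = 1 gives r = 0.94.

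**6. Unequal SDs.** If the Day-29 SD is half the baseline SD, ANCOVA variance relative to change is 0.99/4.20 = 0.24 at r = 0.2 and 0.77/3.00 = 0.26 at r = 0.5. If it is 1.5 times the baseline SD, the ratios are 0.99/1.18 = 0.84 and 0.77/0.78 = 0.99. The comparison with the Day-29 test does not depend on this ratio.

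**The case against.** The strongest reply is that nothing here is invalid. Under 1:1 randomisation the unadjusted t-test is unbiased on average and keeps its overall error rate. The trial calls itself exploratory and claims no power, so no stated figure becomes wrong. This stands, and it limits the severity. A reader might infer from the conditional error rates in step 4 that the planned test inflates type I error. It does not: those rates apply only after an unusually large gap has occurred.

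A reader might also infer that any baseline imbalance passes whole into the result, or that ANCOVA beats both t-tests everywhere. Neither is so. Only a fraction carries over, and at low r a Day-29 test is hardly affected: a gap of 0.33 SD at r = 0.1 shifts it by 0.03 SD. Below r of about 0.17 ANCOVA is marginally less precise than a Day-29 t-test. Entry restricted to 8–15 makes a low r plausible, so this case is realistic. The power contrast of 82% against 66% likewise holds only for a change-score test under an assumed r, effect and equal variances; it is not a statement about this trial's power.

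Finally, 2.13 presents its tests as examples of appropriate methods, and covariate adjustment is often left to an analysis plan, which is not shown here. This weakens the point without removing it: the article does name the between-group test, and the test it names is unadjusted.

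**Conclusion.** The point holds as a should-fix improvement. Section 2.13 fixes an unadjusted between-group test, its repeated-measures ANOVA amounts to the change-score t-test, and the baseline score that would sharpen the comparison is already collected.

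The size depends on r, which the article does not give, and on which score is tested. If the test is on change, as the wording in 2.7 and the Abstract suggests, ANCOVA needs roughly 57–77% of the variance for r from 0.1 to 0.5 with equal SDs; the gain nearly vanishes if the Day-29 SD is 1.5 times the baseline SD and r is 0.5. If the test is on Day-29 scores, the gain is nil or slightly negative below r of about 0.17, about 6% at r = 0.3 and about 23% at r = 0.5. In both cases ANCOVA removes the dependence on the chance baseline gap, assuming a linear relation between baseline and Day-29 scores.

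**What to change.** In 2.13, name a single primary between-group analysis: ANCOVA of Day-29 CIWA-AR on randomised group, with baseline CIWA-AR as covariate, reported as an adjusted mean difference with 95% CI. Keep the t-tests and the repeated-measures ANOVA as supportive only. Make the change before outcome data are seen, since it also settles whether change or final scores are compared.

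The cost is about one sentence and one degree of freedom. SPSS, already named in 2.13, fits this model, and no extra patients, visits or measurements are needed.

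### Within-group paired t-tests and a repeated-measures ANOVA on two time points cannot show an infusion effect; section 2.13 should rest efficacy on one baseline-adjusted between-group comparison

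*Protocol article*

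**What the plan says.** The statistical analysis section (2.13) names three kinds of test. The first two are "paired *t*-tests for within-group comparisons and independent *t*-tests for between-group comparisons, assuming normal distribution of data". The third is "Repeated-measures ANOVA will be applied to assess changes over time in multiple groups based on the nature of data, and outcome measures". One threshold applies to all: "A *p*-value of < 0.05 will be considered significant". The section does not say whether the independent t-test uses the Day-29 score or the change, or which ANOVA effect is meant.

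The outcome section (2.7) names a single outcome: "The major outcome measure is to evaluate the changes in the CIWA-AR score from baseline to Day 28". The rating itself is a day later, according to section 2.6: "On the 29th day, the CIWA-AR scale will be reassessed to evaluate post-intervention changes". The other rating is at Day 0, where section 2.8 says "Eligible patients will be assessed using the CIWA-AR scale". Table 5 has no CIWA-AR rating at week 2; that visit reviews adverse events. So there are two ratings per participant, in two arms of 19 (section 2.9). The Introduction states the aim as a comparison with relaxation techniques alone.

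**The concern.** The aim is comparative, but part of the planned inference is not. Participants enter in mild-to-moderate withdrawal (CIWA-AR 8–15) and are rated again four weeks later. Both arms have daily yoga, meditation and counseling throughout. Improvement without the infusion is therefore to be expected. A paired t-test in the infusion arm, or an ANOVA effect of time, picks up that improvement whether or not the infusion does anything.

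The risk is in the report: a small within-arm p-value, or significance in the infusion arm but not in the control arm, could be presented as efficacy. The between-group tests are also unadjusted, although the baseline score is already collected and adjusting for it costs nothing.

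**Working it through.** **Inputs.** From the article: 19 per arm, ratings at Day 0 and Day 29, threshold 0.05 (two-sided assumed). The article gives no SD, no correlation between the two ratings and no size of natural recovery, so these are assumptions shown as ranges.

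**1. The plan's own error rate.** With no treatment effect, one between-group test should be significant in 5% of trials. Simulation with 19 per arm gives 4.9–5.1% for the change-score t-test, whatever recovery the arms share. The 5% holds for a single between-group test.

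**2. The paired test with no infusion effect.** The noncentrality is √n × (mean fall ÷ SD of change). For a fall of 1 SD of change it is √19 × 1 = 4.36. The critical value of t on 18 degrees of freedom is 2.10. The test is significant about 98% of the time, in each arm.

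For other recoveries shared by both arms, in units of the score SD and with correlations of 0 to 0.7:

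| Shared improvement | Paired test in infusion arm significant |
|---|---|
| 0 | 5% |
| 0.5 SD | 31–76% |
| 1 SD | 83–100% |
| 2 SD or more | about 100% |

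Significance in the infusion arm but not in the control arm occurs in up to about 25% of such trials (0.5 SD, correlation 0.5).

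**3. What the ANOVA adds.** With two time points, the group-by-time term compares mean change between arms, so F = t² of the change-score t-test. A numerical example gave 0.01992 for both. This term is redundant. The time effect has the defect shown in step 2.

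**4. Claiming more than one between-group result.** No treatment effect, correlation 0.1–0.5:

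| Counted as efficacy if significant | Baseline SD equal to Day-29 SD | Baseline SD half of Day-29 SD |
|---|---|---|
| Day-29 or change t-test | 8.4–9.1% | about 7% |
| Either of these, or the ANOVA group effect | 11–12% | about 9% |

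The half-SD column matters because eligibility restricts the baseline score to 8–15.

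**5. What baseline adjustment offers.** Take a true difference of 0.93 Day-29 SDs, correlation r = 0.3 and equal SDs. The SD relevant to each analysis, in units of the Day-29 SD, is:
- Day-29 t-test: 1, so the standardized difference is 0.93; power 80%.
- Change t-test: √(2(1 − r)) = √1.4 = 1.18, so 0.93 ÷ 1.18 = 0.79; power about 66%.
- ANCOVA: √(1 − r²) = √0.91 = 0.95, so 0.93 ÷ 0.95 = 0.98; power about 82%, error 5%.

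The gain over the Day-29 test is small and nearly vanishes at low correlation (r = 0.1: √0.99 = 0.995). The gain over the change score vanishes when the regression slope r × (Day-29 SD ÷ baseline SD) equals 1, for example 0.5 × 2. ANCOVA therefore comes close to the better of the two without knowing the correlation beforehand.

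**The case against.** The strongest reply is that the article already points to the right test. It names one outcome, the change in CIWA-AR, and its aim is comparative. Section 2.13 gives the paired tests a within-group role and the independent tests a between-group role. Read together, the between-group test on change answers the question and holds 5%. This stands: a reader might infer that the plan's error rate does exceed 5%, and the text does not support that. The excess arises only if more than one result may be claimed as efficacy, which the article neither states nor rules out.

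Two further inferences also fail. One is that the ANOVA is itself an error; its group-by-time term is redundant and harmless. The other is that the trial would lose much power through the ANOVA group main effect, which averages the pre-treatment score with the Day-29 score and has about 41% power under the step 5 assumptions. The article never says it will use that effect; the purpose it gives is change over time.

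Nor is the lack of a named decisive test a finding by itself. An article may leave that to an analysis plan, and none is shown here.

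The exploratory label carries less weight. It softens a strict error-rate argument, but the Conclusion still expects clinical evidence of therapeutic efficacy, and a significance threshold is set. A within-arm comparison cannot separate the infusion from recovery in an exploratory trial any more than in a confirmatory one.

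**Conclusion.** The point holds in a limited form. The within-group tests and the ANOVA time effect are unsuitable for the stated comparison, and with an assumed shared fall of 1 SD of change each paired test is significant about 98% of the time with no infusion effect. The group-by-time term adds nothing to the change-score t-test. An error rate above 5% among between-group tests is a conditional risk of about 7–12%, not a property of the plan as written. A baseline-adjusted comparison is a better use of the data already collected, with modest or no gain depending on the correlation. The percentages rest on normal data and on assumed recovery, correlation and SD ratio; the direction of the within-group problem requires only that both arms improve.

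**What to change.** In section 2.13:
- State that the one efficacy inference is the between-group difference in Day-29 CIWA-AR, adjusted for baseline CIWA-AR by ANCOVA, with its 95% CI.
- Report within-group changes descriptively, for example as means with SDs, and not as evidence of efficacy.
- Drop the repeated-measures ANOVA as redundant with two ratings, or label it supportive.

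This is a change of wording. It needs no further visits, ratings or participants. The cost is that within-group p-values can no longer be presented as findings.
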